### Active online control condition (program for healthy nutrition)

The online control intervention focuses on healthy nutrition (a topic that has no direct link to the intervention addressing stress management and MHL). It can be used according to individual needs and preferences and aims to educate C&A on the following topics about nutrition in order to promote healthy eating: (1) Basics about healthy nutrition, nutrients and energy; (2) Fruit and vegetables; (3) Breads, cereals, and potatoes; (4) Milk, dairy products, fish, meat, sausages, and eggs; (5) Healthy drinks; (6) Many different foods, enjoy the diversity of foods available; (7) Healthy breakfast and healthy snacks; (8) Eating when you are out. All contents are based on recommendations provided by the German Society for Nutrition [35]. The technical functions are parallel to the online intervention *StresSOS* with the exception that there will be no group chat.

### Sample size calculation

In the control condition, 30% transitions from “healthy” to “at-risk” are expected. Further, it is anticipated that participation in *StresSOS* (online or face-to-face) will prevent 50% of these transitions, i.e., reduce the transitions to 15%. The sample size calculation is primarily based on the non-inferiority trial (Study B). Assuming equal efficacy for online and face-to-face delivery of *StresSOS* (i.e., 15% transition to “at-risk”), a non-inferiority margin δ = 5%, and an allocation ratio of 5:1, 2920 participants (2500 in the online and 420 in the face-to-face condition) need to be included in Study B to test non-inferiority with 80% power at α = 5% (Z-test). For Study A, the proposed sample size will allow one to assess the assumed group differences precisely (95% confidence interval (CI) +/− 2.3%); i.e., it allows one to test clinical significance of the efficacy of online *StresSOS* (between-group difference > 10%) with more than 95% power. The sample size may be larger, as all C&A who do not meet the inclusion criteria of the other four ProHEAD trials for C&A with (sub-threshold) mental health problems [31–34] are included. Even if the proposed sample size is reached, the program will still be offered to “healthy” C&A.

Based on previous experiences in school-based settings, there may be an expected loss to follow-up rate of 15% for the face-to-face sample [36] and 25% for the program-specific assessments of the online sample. Based on the literature [19] and the experiences within the consortium, the expectation is that about 33% of the participants in the online *StresSOS* condition will be compliant and work through the modules as expected, 33% will utilize about half of the modules, and 33% will log in only once.

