**Discussion:**

This study represents the first adequately powered non-inferiority trial in the area of school-based mental health promotion. If online *StresSOS* proves efficacious and non-inferior to face-to-face delivery, this offers great potential for health promotion in youths, both in and outside the school environment.

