#### Study B

Non-inferiority [56] of online delivery of *StresSOS* will be tested against the null hypothesis H0: Difference (% transitions face-to-face – % transitions online) < 5% (Z-test, α = 5%). Non-inferiority is assumed if the upper limit of the 95% CI of the empirical group difference is less than 5% (CI inclusion approach). Propensity score weighting methods will be applied to control for potential confounders between the online and the face-to-face condition [57]. The covariates taken into account for the propensity score procedure will be, for example, psychological strain, coping skills, age, gender, and type of school. Tests will be based on ITT principles; missing values will be imputed.

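### Study B: the Z-test at α = 5% and the 95% CI rule do not clearly work at the same level; under a two-sided 95% CI, plain Z-test power at 2500/420 is about 76% (about 70% after the stated face-to-face loss), not 80%, and 2500:420 is not 5:1

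*Protocol article*

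**What the plan says.** The Sample size calculation section bases the trial mainly on Study B. Its inputs are:

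- Rates: "Assuming equal efficacy for online and face-to-face delivery of *StresSOS* (i.e., 15% transition to “at-risk"). The 30% expected in the control condition belongs to Study A and does not enter here.
- Margin and ratio: "a non-inferiority margin δ = 5%, and an allocation ratio of 5:1".
- Size: "allocation ratio of 5:1, 2920 participants (2500 in the online and 420 in the face-to-face condition").
- Power and level: these participants "need to be included in Study B to test non-inferiority with 80% power at α = 5% (Z-test"). No sidedness is given.

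A separate paragraph of the same section adds that "there may be an expected loss to follow-up rate of 15% for the face-to-face sample". It also gives 25% for the online sample, but for the program-specific assessments. It does not say whether 420 already allows for loss.

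The Study B analysis section repeats the Z-test at α = 5%, again without sidedness, and then sets the decision rule: "Non-inferiority is assumed if the upper limit of the 95% CI of the empirical group difference is less than 5" per cent. It plans an ITT analysis with imputation. The Study A section, by contrast, labels its test two-sided.

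The abstract concludes: "This study represents the first adequately powered non-inferiority trial in the area of school-based mental health promotion". The main Discussion repeats the claim.

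**The concern.** A non-inferiority test looks at one side only. Comparing the upper limit of a two-sided 95% CI with the margin is a test at one-sided 2.5%; a one-sided 5% test pairs with a 90% CI. The plan names a 5% Z-test and a 95% CI for the same hypothesis and says of neither whether it is one- or two-sided. The reader therefore cannot tell whether the risk of wrongly declaring non-inferiority is capped at 2.5% or 5%, and a result near the boundary could pass one criterion and fail the other.

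Power depends on the same choice. Study B drives the sample size and supports the claim of adequate power, so if 80% belongs to one level and the decision is taken at the other, the claim does not describe the trial as planned. The printed ratio and the printed arm sizes also disagree, so the calculation cannot be followed from its own inputs.

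**Working it through.** **Inputs** (all from the Sample size calculation section): rate 0.15 in both arms, true difference 0, margin 0.05, arms 2500 and 420, face-to-face loss 15%, so 420 × 0.85 = 357.

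**Formula** (plain Z-test, unpooled variance, independent observations):

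SE = √[0.15 × 0.85 × (1/n_online + 1/n_f2f)], power = Φ(0.05/SE − z), with z = 1.645 at one-sided 5% and z = 1.96 at one-sided 2.5%. The two rates are equal, so the sign convention for the difference does not affect this result.

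**Results**

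| Evaluable online / face-to-face | SE | 0.05/SE | Power, one-sided 5% | Power, one-sided 2.5% |
|---|---|---|---|---|
| 2500 / 420 (no loss) | 0.01883 | 2.655 | 84.4% | 75.7% |
| 2500 / 357 (15% face-to-face loss) | 0.02020 | 2.475 | 79.7% | 69.7% |

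**The plan's own 80%.** The plain formula reproduces it at one-sided 5% with 357 evaluable face-to-face pupils and no online loss (79.7%). A second route, also at one-sided 5%, uses 2500/420 with no loss and the variance under a null of 15% online and 20% face-to-face (79.95%). At one-sided 2.5% these two routes give 69.7% and 68.9%.

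**Where the two criteria part.** Taking SE = 0.01883 as a guide, the one-sided 5% Z-test passes if the observed excess of transitions online is below 0.05 − 1.645 × 0.01883 = 0.0190. The two-sided 95% CI rule passes only below 0.05 − 1.96 × 0.01883 = 0.0131. An excess between about 1.3 and 1.9 percentage points would get opposite answers.

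**Other variance estimators at one-sided 2.5%** (score and Newcombe taken for online minus face-to-face):

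| Method | 2500 / 420 | 2500 / 357 |
|---|---|---|
| Wald CI, exact enumeration | 77.2% | 71.0% |
| Score test | 81.5% | 76.7% |
| Newcombe CI, exact enumeration | 81.8% | 76.9% |

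**Ratio.** 2500/420 = 5.95. A true 5:1 would be 2500:500 or 2100:420. Splitting the total of 2920 at 5:1 gives 2433/487, and plain power at one-sided 2.5% is then 80.5% with no loss. With 487 × 0.85 = 414 face-to-face it is 75.0%. Keeping 420 at 5:1 (2100/420, no loss) gives 74.5%.

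**Size for 80% under the two-sided 95% CI rule with 2500 online.** The required SE is 0.05/(1.96 + 0.8416) = 0.01785. This gives 1/n_f2f = 0.01785²/0.1275 − 1/2500, or about 477 evaluable, which is 477/0.85 ≈ 562 enrolled at 15% loss.

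**The case against.** The plan never calls the Study B interval two-sided, and only its upper limit is used. A one-sided 95% upper limit would agree with a one-sided 5% test and remove the conflict. That is possible, and it makes this an ambiguity rather than a proven clash. But elsewhere the article uses 95% CIs in the ordinary sense: a symmetric ± 2.3% in the sample size section, and an interval beside a two-sided test in Study A. A reader will take the Study B interval the same way unless told otherwise. If instead α = 5% is meant as two-sided, test and interval do agree, but plain power at the stated arms is then 75.7%.

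A reader might infer that 80% can be reached only at one-sided 5%. The figures do not support that. With no loss, a score test at 2500/420 gives 81.5% and a 5:1 split of 2920 gives 80.5%, both at one-sided 2.5%, and the article names no variance estimator. Nor is it established that the sample size was computed at the more lenient level. The match at 79.7% needs a deduction for loss that the article does not say was made; without it the same formula gives 84.4%.

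These points do not restore 80% once the stated loss is counted. At one-sided 2.5% with 357 face-to-face pupils, the plain, exact Wald, score and Newcombe versions run from 69.7% to 76.9%. One formula does exceed 80% there: using the variance of a null with 15% online and 10% face-to-face throughout gives 81.9%. That variance is smaller than the one at the assumed 15% in both arms; with the latter in its proper place the figure is 78.4%.

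Imputation is planned, so treating loss as a plain reduction in numbers is an approximation. Imputed values do not generally restore the information lost.

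**Conclusion.** The point holds in this form. The plan should say which one-sided level governs Study B. Under the ordinary reading of a 95% CI, the stated 80% is not delivered by a plain Z-test at the stated arm sizes: power is about 76% with no loss and about 70% with 15% face-to-face loss. A score test would give about 81.5% and 77%. At one-sided 5% the plain figures are 84% and 80%. The 5:1 ratio is inconsistent with 2500:420 on any reading.

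Two stronger conclusions should not be drawn. First, 70% is not the effect of the interval level alone; that change takes 84.4% to 75.7%, and the rest is attrition. Second, a figure of 67.9%, obtained by also removing 25% of the online arm (1875/357), is not supported: the 25% is stated for the program-specific assessments, while the primary outcome comes from the school-based follow-ups.

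The figures assume 15% transitions in both arms, independent observations and no weighting. Whole-class recruitment in the face-to-face arm and propensity weighting would probably lower power further and are not counted here.

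**What to change.** State one one-sided level for Study B and use it in the test, the interval and the sample size. Either:

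- keep the two-sided 95% CI as the single rule, describe the Z-test as one-sided 2.5%, and restate plain Z-test power as about 76% without loss and about 70% with 15% face-to-face loss; or
- if one-sided 5% is intended, write a 90% CI or a one-sided 95% upper limit into the decision rule.

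In both cases, name the variance estimator, restating the power to match if it is not the plain one, and say whether 420 already includes attrition. Correct the ratio to about 6:1, or correct the arm sizes if 5:1 was meant. If the 95% CI rule is kept with the present numbers, qualify the claim of adequate power in the abstract and the Discussion.

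The cost is wording in the protocol and analysis plan, best settled before outcome data are seen. The first option makes the stated power less favourable; the second accepts a 5% rather than 2.5% risk of a false non-inferiority claim. Only if the sponsor wants 80% under the two-sided 95% CI with the plain test does the sample change, to about 477 evaluable face-to-face pupils with 2500 online.

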### Measures

#### Primary outcome measures

The primary outcome is the number of C&A with transition from the “healthy” group to the “high-risk” or the “mental health problems” group at 12 months follow-up, i.e., the proportion of C&A fulfilling any of the criteria for at-risk C&A or for C&A with mental health problems outlined in the ProHEAD trials on general mental health problems, eating disorder symptoms, at-risk alcohol use, and depressive symptoms (see [31–34] in this issue). Data will be assessed in the school-based follow-ups at 1 and 2 years post-enrollment within the ProHEAD Consortium.

The measures include the following instruments. The *Strengths and Difficulties Questionnaire* (SDQ) [37] is a screening questionnaire for psychosocial problems in C&A. It comprises four sub-scales (emotional, conduct, hyperactivity, and peer problems), each scored on a scale from 0 to 10. Instruments specific for the assessment of eating disorder symptomatology include the *Short Evaluation of Eating Disorders* (SEED) [38] and the *Weight Concerns Scale* (WCS) [39]. The SEED assesses the three main symptoms for anorexia (degree of underweight, fear of weight gain, and distortion of body perception) and bulimia (amount of binge eating, amount of compensatory behavior, and over-concern with body shape and weight). The WCS uses five items to assess concerns with weight associated with body image in women. Instruments specific for the assessment of risky alcohol use and alcohol misuse include the *Car, Relax, Alone, Forget, Friends, Trouble* questionnaire (CRAFFT-d) [40] and the *Alcohol Use Disorders Identification Test* (AUDIT) [41]. The CRAFFT-d is a behavioral health screening tool for at-risk alcohol use. The AUDIT is a screening tool developed by the WHO to assess alcohol consumption, drinking behaviors, and alcohol-related problems. As the main instrument for the assessment of depressive symptoms, the *Patient Health Questionnaire-9 modified for Adolescents* (PHQ-A) [42] is used. The PHQ-A is a nine-item self-report instrument assessing the presence and severity of depressive symptoms based on the diagnostic criteria for depression according to the Diagnostic and Statistical Manual of Mental Disorders, fourth edition (DSM-IV) [43].

#### Secondary outcome measures

In addition, assessments will be performed related to stress/coping (i.e., knowledge, symptoms of stress, coping resources), self-esteem, MHL (knowledge and attitudes about mental disorders and help-seeking), program usage patterns, cost of programs, and acceptance of the intervention. Data will be assessed in the school-based follow-ups at 1 and 2 years post-enrollment within the ProHEAD Consortium, except for the assessments related to knowledge, self-esteem, symptoms of stress, and coping resources, which will take place at the trial-specific post-line.

Knowledge about stress/coping and mental health will be assessed with a multiple-choice questionnaire (pretested in a pilot study with adolescents) measuring knowledge about stress (stressors, stress response, stress appraisals), different coping strategies and their implications (problem-solving, cognitive reconstruction, relaxation, seeking support), mental health/illness, and help-seeking. Symptoms of stress and coping strategies will be assessed using the *Stress and Coping Questionnaire for Children and Adolescents* (SSKJ 3–8 R) [44]. The physical symptoms scale consists of six items (e.g., headache, stomach ache; referring to the last week). With regard to coping, only the items related to coping with a social peer problem situation will be used with five-item sub-scales related to seeking social support, problem-solving, avoidant coping, and electronic media use. To assess self-esteem, the *Inventory of Self-Esteem for Children and Adolescents* (SEKJ) [45] will be used, applying the scales height and stability of self-esteem.

Three instruments are used to cover help-seeking intentions, actual help-seeking behavior, and attitudes toward help-seeking. The *General Help-Seeking Questionnaire* (GHSQ) [46] is a self-report measure of help-seeking intentions for selected mental health problems. The *Actual Help-Seeking Questionnaire* (AHSQ) [47] assesses actual help-seeking behavior by listing potential help sources and measuring whether or not help has been sought from the respective sources within a specified time period for a specified problem. It comprises three sub-scales: whether or not informal help has been sought, whether or not formal help has been sought, and whether no help has been sought. Further, the *Inventory of Attitudes Toward Seeking Mental Health Services* (IASMHS) [48] has three internally consistent factors: psychological openness, help-seeking propensity, and indifference to stigma. To assess barriers of help-seeking, the short form of the *Barriers to Adolescents Seeking Help Scale* (BASH-B) [49], including 11 items, will be used. Further, items from the *Questionnaire on Social Distance* [50], assessing stigma toward peers affected by mental health problems, will be used.

Participants will be asked to indicate their overall *program acceptance*; C&A provide an overall evaluation of the program and indicate whether they have learned something from it, and if they would recommend the program to friends or other adolescents. *Program user statistics* regarding the online intervention will be collected based on the system’s log files.

Health care utilization of participants will be collected by the *Mannheimer Modul Ressourcenverbrauch* (MRV), a scale that lists all possible health care services for a given study sample or risk group and reports the frequency of usage (e.g., visits, drug intake, hospital days) over a given period of time [51]. Similar scales are applied in international cost studies [52]. The MRV was modified and pretested for use in an adolescent population.

Health-related quality of life will be assessed using the *KIDSCREEN-10* [53]. The KIDSCREEN is an international cross-culturally comparable quality of life assessment instrument tailored for C&A aged 8 to 18 years.

#### Other measures

Sociodemographics (i.e., gender, age, migrant status, socioeconomic status, etc.) will be assessed. For assessment of personality disorders, the *Standardized Assessment of Personality – Abbreviated Scale* (SAPAS) [54] will be used. The SAPAS is a self-report questionnaire consisting of eight items that screen for personality disorders. Figure 2 displays an overview of enrollment, interventions, and measures used as well as the corresponding time of assessment.

**Fig. 2 Fig2:**
[figure not shown]
Schedule of enrollment, interventions, and assessments. Note: *SDQ* Strengths and Difficulties Questionnaire, *SEED* Short Evaluation of Eating Disorders, *WCS* Weight Concerns Scale, *PHQ-A* Patient Health Questionnaire-9 modified for Adolescents, *CRAFFT-d* Car, Relax, Alone, Forget, Friends, Trouble, *AUDIT* Alcohol Use Disorders Identification Test, *GHSQ* General Help-Seeking Questionnaire, *AHSQ* Actual Help-Seeking Questionnaire, *IASMHS* Inventory of Attitudes Towards Seeking Mental Health Services, *BASH-B* Barriers to Adolescents Seeking Help Scale, *MRV* Mannheimer Modul zum Ressourcenverbrauch, *KIDSCREEN-10* Health-related quality of life, *SSKJ 3–8 R* Stress and Coping Questionnaire for Children and Adolescents, *SEKJ* Inventory of Self-Esteem for Children and Adolescents. *Participants will complete the ProHEAD baseline screening and 1 and 2year follow-up assessments within the ProHEAD Consortium. In addition, assessments within the *StresSOS* trial will be conducted at baseline and post-intervention (8 weeks after onset of intervention)

### Statistical analyses

#### Study A

Differences in the transition rate from the “healthy” group to the “high-risk” or the “mental health problems” group at 12 months follow-up will be tested with Fisher’s exact test (two- sided, α = 5%). The 95% CIs for the group difference will be calculated in order to test clinical significance (> 10% difference) of the online *StresSOS* efficacy. Analyses will be based on intention-to-treat (ITT) principles. Missing values will be imputed with the predictive mean matching method using the R package mice (Multivariate Imputation by Chained Equations [55]).

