### Enrollment and randomization

Permission to contact schools within the regional districts of all five recruiting study sites (Hamburg, Heidelberg, Leipzig, Marburg, Schwäbisch Gmünd) will be requested from federal authorities. A total list of schools in the regional districts will be acquired. Eligible schools will be contacted and informed, in random order, about the possibility to participate, until the prospected sample size is reached (in total *N* = 15,000 C&A). Following the baseline screening, healthy C&A (not fulfilling allocation criteria for any other ProHEAD program; see [31–34]) will be invited to participate in the *StresSOS* online program. C&A will receive an email including information about the trial and access details for the baseline assessment within the *StresSOS* trial. After completing this assessment, participants will be randomized with equal probability (in a 1:1 ratio) to the online *StresSOS* program and the online control group (online program on healthy nutrition). The allocation will be randomized, stratified for gender and school type. Randomization will be conducted externally and will follow a permutated block design with variable, randomly arranged block sizes. Following randomization, participants will be contacted informing them about their allocation to the respective intervention group and will receive access details for the specific online program.

In the face-to-face *StresSOS* program, the entire class will be invited to participate in the trial. Parallel to the online trial, eligible schools will be contacted and informed in random order about the possibility of participating in the program. Blinding is not possible. Participating C&A and experts are not unaware of the interventional procedure. However, assessments are based on self-report and take place within the school-based screening, which helps to avoid biased assessment of results.

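### Study A's primary test ignores the randomisation strata and gives nothing that Rubin's rules can pool directly; a stratum-adjusted risk difference would match both the design and the imputation

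*Protocol article*

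**What the plan says.** In the protocol article, the section Enrollment and randomization sets a 1:1 ratio between online StresSOS and the online control, and adds: "The allocation will be randomized, stratified for gender and school type".

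Under Statistical analyses, Study A, the transition rates "at 12 months follow-up will be tested with Fisher’s exact test", two-sided at 5%. No stratification factor or covariate is attached to that test. The same paragraph plans a 95% confidence interval for the group difference, to be judged against a 10-point threshold. It also plans an intention-to-treat analysis with imputation: "Missing values will be imputed with the predictive mean matching method using the R package mice". It gives neither the number of imputations nor a rule for combining results.

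For Study B, gender and type of school are listed among the example covariates for the propensity score.

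**The concern.** The named test does not fit two choices made elsewhere in the plan.

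- **Strata.** Stratified allocation balances gender and school type across the arms. If these factors predict transition, the balance makes the difference between arms less variable than an unstratified test supposes. The test is then conservative and gives up some power.
- **Imputation.** Rubin's rules combine an estimate and its standard error across completed data sets. Fisher's test returns only a p-value. The planned interval for the difference fits the imputation, but the planned test does not fit it directly.

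At stake are some efficiency and a primary p-value that comes from a different route than the interval reported beside it. The validity of the trial is not at stake.

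**Working it through.** **1. The plan's own figures (Sample size calculation).** Inputs: "In the control condition, 30% transitions from “healthy” to “at-risk” are expected"; StresSOS "will prevent 50% of these transitions, i.e., reduce the transitions to 15"%; 2,500 in the online StresSOS arm, hence 2,500 controls at 1:1.

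- SE = √(0.30×0.70/2500 + 0.15×0.85/2500) = √0.000135 = 0.01162
- Half-width = 1.96 × 0.01162 = 2.28 points (stated: 2.3)
- Power for a difference above 10 points = Φ((0.15 − 0.10)/0.01162 − 1.96) = Φ(2.34) = 99.0% (stated: more than 95%)

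Both figures reproduce. With 25% fewer participants (1,875 per arm) they become 2.63 points and 96.1%.

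**2. Effect of ignoring the strata.** The article gives no transition rates by stratum, so these are assumptions: six equal strata, 417 per arm in each (2,502 per arm), mean rate 30%. Fisher's test and a Cochran–Mantel–Haenszel (CMH) test were applied to the same simulated trials. There were 20,000 runs, so the simulation error on a 5% rate is √(0.05×0.95/20000) = 0.15 points. The small effect is a 13% relative reduction (30% to 0.87 × 30% = 26.1% on average).

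| Assumed stratum rates | Type I error, Fisher | Type I error, CMH | Power at small effect, Fisher | Power at small effect, CMH |
|---|---|---|---|---|
| 30% in all | 4.8% | 5.2% | 86.1% | 86.8% |
| 15% to 45% | 3.9% | 4.6% | 86.7% | 88.6% |
| 5% to 55% | 3.3% | 5.3% | 87.8% | 91.0% |

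At the planned halving of risk (2,000 runs), both tests had about 100% power in all three settings.

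The 0.7-point gap in the first row arises where the strata do not predict the outcome. It therefore reflects the conservatism of Fisher's test itself, not the strata.

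A hand check supports the other two rows. With rates of 15, 21, 27, 33, 39 and 45%, the between-stratum variance is 2 × (0.15² + 0.09² + 0.03²)/6 = 0.0105. The true variance is then (0.21 − 0.0105)/0.21 = 0.95 of what an unstratified test assumes. The error of an unstratified z-test is 2 × (1 − Φ(1.96/√0.95)) = 4.4%. With 5% to 55%, the between-stratum variance is 2 × (0.25² + 0.15² + 0.05²)/6 = 0.0292, the ratio is 0.861, and the error is 3.5%. Fisher's own conservatism lowers these a little further.

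**3. Pooling after imputation.** Assumptions: 25% of outcomes missing at random, no auxiliary predictors, 20 imputations, 2,500 per arm, both arms truly at 30%. There were 3,000 runs (simulation error 0.4 points).

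- Rubin's rules on the risk difference, T = W + (1 + 1/m)B: type I error 4.9%
- Fisher p-values turned into z-scores, with mean z divided by √(1 + (1 + 1/m) × var(z)): 4.7%

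At 30% v 26% the two had similar power (79.4% and 79.0%). A workable rule for Fisher's test therefore exists. It is an extra device that the risk difference does not need.

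**The case against.** The strongest reply is that nothing planned for Study A is endangered. Ignoring the strata makes the test conservative, not invalid. The larger losses need strong assumed differences between strata and an effect far below the one planned. The number of imputations and the combining rule are details that a condensed article may leave to a full protocol or analysis plan that is not shown. All of this stands, and it limits the point to efficiency and coherence.

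A reader might infer more in three ways, none of which the document supports.

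- **That the test cannot be pooled or computed.** It can, after z-transformation, and the planned interval pools directly. That the imputation is multiple is itself inferred from the choice of mice.
- **That the primary error rate is inflated.** In the simulation above, Fisher's test on one completed data set had 12.8% type I error, which corresponds to interval coverage of about 87%. But the article does not say that a single data set will be analysed or that predictors will be left out. Its 25% loss figure refers to the programme-specific online assessments, whereas the primary outcome comes from the school-based follow-ups, for which no online loss rate is given.
- **That the test and the interval for clinical significance may conflict.** They address different nulls, zero and 10 points. At the planned precision, an interval lying wholly above 10 points needs an estimate above about 10 + 2.28 = 12.28 points, which is 12.28/1.162 = 10.6 standard errors from zero. A significant test with an interval that includes 10 points is no contradiction.

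What remains is that the article does more than leave a gap: it names a test, and that test sets aside the stratification factors.

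**Conclusion.** The point holds as a modest improvement to a stated method. The unstratified Fisher's test is somewhat conservative if gender and school type predict transition: type I error is 3.9% or 3.3% under the two assumed sets of prognostic stratum rates. Compared with a stratified test it gives up 0.7 to 3.2 points of power at a 13% relative reduction. The lower figure applies even to non-prognostic strata. At 30% v 15% nothing is lost, and the stated precision and power for Study A stand.

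The test also has no direct Rubin's-rules form, although workable alternatives exist. The size of the loss rests on assumed stratum rates and six equal strata. It matters only if the true effect is well short of the planned halving.

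**What to change.** Make the Study A primary analysis a risk difference stratified by or adjusted for gender and school type. Use either Mantel–Haenszel or logistic regression with standardisation, and name one in advance. Baseline SDQ and PHQ-A may be added under the regression option. Their gain has not been quantified and may be small, because participants are screened as healthy and the range of these scores is restricted.

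Estimate the difference in each imputed data set and pool by Rubin's rules. Take both the two-sided 5% test and the 95% interval for the 10-point threshold from this one pooled analysis. Keep Fisher's test as a sensitivity analysis.

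The cost is a documented change of wording to the published primary test, made before outcome data are seen. The stratification factors are already needed for randomisation, and neither the sample size nor data collection changes.
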